**Kidney donor inclusion criteria**
A prospective donor is eligible if all of the following inclusion criteria apply:Eligible for live kidney donation.Aged at least 18 years.ABO blood group compatible with the organ recipient.Willing to provide personal, medical and biological data for the trial analysis.Willing and able to provide a blood sample for the immune monitoring assays.Willing and able to give informed consent for participation in the trial.
**Kidney donor exclusion criteria**
If a prospective donor fulfils any of the following criteria, they are ineligible for the trial:Exposure to any investigational agents at the time of kidney donation, or within 28 days prior to kidney donation.Any form of substance abuse, psychiatric disorder or other condition that, in the opinion of the investigator, may invalidate communication with the investigator designated personnel.Is a paired exchange donor.Is an altruistic donor.

### Control arm

Participants in the control arm undergo planned living donor kidney transplantation with a standard basiliximab (anti-CD25) based immunosuppression protocol (figure 1). Briefly, patients will be preloaded with tacrolimus starting 4 days prior to transplantation and continued long-term aiming for trough levels of 3–10 ng/mL. On the day of transplant patients commence mycophenolate mofetil at an initial maintenance dose of 1000 mg two times a day. Intravenous methylprednisolone 500 mg and intravenous basiliximab 20 mg are administered at induction. On day 1 post transplant 125 mg of intravenous methylprednisolone is administered before ongoing oral prednisolone commences at 20 mg one time a day on day 2. A further 20 mg of intravenous basiliximab is given on day 4 post transplant. Maintenance immunosuppression on discharge thus consists of tacrolimus aiming for trough levels of 3–10 ng/mL, mycophenolate mofetil 1000 mg two times a day and prednisolone 20 mg one time a day. Mycophenolate mofetil is reduced to 500 mg two times a day from 14 days post transplant and continued long-term. Prednisolone is weaned to stop over 14 weeks resulting in dual maintenance therapy with mycophenolate mofetil and tacrolimus. Immunosuppression regimens and dose reductions in both arms are summarised in figure 2.

**Figure 2 F2:**
[figure not shown]
Overview of maintenance immunosuppression dosing with minimisation in the TR001 (cell therapy) arm.

### TR001 arm

Patients recruited to the cell therapy arm attend for venesection of 370 mL of whole blood a minimum of 3 weeks prior to planned transplantation to permit manufacture of the autologous Treg product (TR001). Following transport to the good manufacturing practice unit at Guy’s and St Thomas’ Hospital, London, whole blood undergoes negative selection of CD8^+^ cells and positive selection of CD25^+^ cells resulting in enrichment of CD4^+^CD25^+^FOXP3^+^ Treg (approximately 75% of total cells entering the expansion phase). Polyclonal expansion of cells is achieved through up to three rounds of stimulation with anti-CD3 and anti-CD28 bead stimulation in the presence of IL-2. Importantly, rapamycin is added to the culture conditions and has been shown to promote Treg stability and preferential expansion over contaminant populations. Full details of the expansion protocol have been described elsewhere.^17^ Following expansion, the final cell product is cryopreserved at a dose of 5–10×10^6^ cells/kg body weight of the intended recipient in preparation for future infusion.

Living donor kidney transplantation occurs in line with standard clinical practice but with minimisation of immunosuppression from the outset in the TR001 arm. Initial maintenance immunosuppression with tacrolimus (Envarsus, Chiesi is the preferred long-acting sustained release formulation in both arms to avoid Treg toxicity that may occur at peak concentrations), mycophenolate mofetil and prednisolone is provided in an identical manner to those participants in the control arm. Importantly, where basiliximab is administered to control patients, those in the TR001 arm will receive no monoclonal induction agent at the time of transplantation. On day 5 post-transplant patients in the TR001 arm receive an infusion of 5–10×10^6^ cells/kg of thawed autologous polyclonal Tregs administered in 100 mL of 5% human albumin solution.

Planned reduction of maintenance immunosuppression in the TR001 arm will be dependent on stable biochemical transplant function. In the TR001 arm, protocol biopsies are performed for monitoring purposes at 22 weeks and 38 weeks post transplant. Target trough tacrolimus levels are reduced from 3 to 10 ng/mL to 3–6 ng/mL at week 38 once biopsy results have been received. The maintenance dose of mycophenolate mofetil will be reduced to 250 mg two times a day from week 37 post transplant and stopped at 48 weeks post transplant such that patients will subsequently continue on low-dose tacrolimus monotherapy as long-term maintenance (figure 2).

### Primary outcome

The primary outcome is incidence of biopsy-confirmed acute rejection (BCAR) in the 18 months post transplantation. A diagnosis of BCAR can be made based on protocol driven or clinically indicated ‘for cause’ biopsies. ‘For cause’ biopsies may be performed during follow-up at the discretion of the responsible clinician taking into account the full clinical picture and are typically triggered by an unexplained rise in serum creatinine as per standard National Health Service (NHS) practice. Whenever rejection is suspected, a for-cause graft biopsy will always be offered and performed with the patient’s permission. The results of for-cause biopsies will be available to the trial investigators and the outcome will be documented in the electronic database.

All biopsies performed will be reviewed and reported by the study pathologist using the internationally accepted Banff criteria. Whenever a biopsy is reported as suspicious for rejection or borderline changes, responsibility for a diagnosis of rejection lies with the treating physician.

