**Figure 1 F1:**
[figure not shown]
Diagrammatic representation of the immunosuppressive regimen used in The TWO study.

Participants will be approached and enrolled by the clinical principal investigator (PI) or deputy following approval of listing for living donor kidney transplantation by the clinical multidisciplinary team meeting. Randomisation is computer generated and performed by minimisation, with stratification for ethnicity and Human Leukocyte Antigen - DR (HLA-DR) mismatch. Treatment allocation will be open-label as pre-transplant venesection of blood for Treg manufacture in those allocated to the TR001 arm is required and it is not ethically appropriate to perform venesection in control patients prior to major surgery. Accordingly, outcome assessors and statisticians are not blinded.

With a relatively small patient sample size, the emergence of significant numbers of patient discontinuation in the trial may obscure the true outcome of this research. Discontinued participants may be replaced by the recruitment of additional patients. The decision to replace individual patients will ultimately be made by the clinical PI on the basis that some unanticipated factor may influence the clinical outcome in terms of the primary endpoint.

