Assays will be performed to investigate whether cell therapy shifts kidney transplant recipients towards a more tolerance-prone phenotype or away from a rejection-prone phenotype. Gene expression of a defined set of tolerance-associated genes in whole blood will be profiled by quantitative PCR. Leucocyte subset profiling will be performed by flow cytometry to quantify immune cell subpopulations in patient peripheral blood. Donor-reactive T cell frequencies will be measured following co-culture of recipient T cells with stored donor derived antigen presenting cells using a CD154/137 assay. This assay will be performed before and after transplantation to enable an estimation of the pre-transplant frequency of donor-reactive T cells, and detection of post-transplant sensitisation against donor antigen. Treg frequencies in patient blood will be measured by epigenetic analysis of the Treg-specific demethylated region of the FOXP3 gene. Finally, cytokine and metabolic profiling will be performed assessing inflammatory and regulatory cytokines as well as low-molecular-weight metabolites to provide a picture of the dynamic changes that may take place in the immune response after cellular therapy and immunosuppression modification.

Histopathological samples will be taken at 5 months (protocol biopsy) in kidney transplant recipients randomised to the TR001 arm. This biopsy will confirm the ongoing safety of Treg therapy and ensure no evidence of subclinical rejection. A 9-month protocol biopsy will be performed in all participants including the control arm to allow a histological comparison of the impact of Treg therapy.

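### Rejection on protocol biopsies counts towards the primary endpoint, but only TR001 has a 22-week protocol biopsy, so the between-arm comparison mixes treatment effect with unequal detection

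*Protocol article*

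**What the plan says.** The Primary outcome section fixes the endpoint: "The primary outcome is incidence of biopsy-confirmed acute rejection (BCAR) in the 18 months post transplantation". It then states which biopsies can establish an event: "A diagnosis of BCAR can be made based on protocol driven or clinically indicated" for-cause biopsies.

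Two sections give the schedule of protocol biopsies.

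- TR001 arm: "In the TR001 arm, protocol biopsies are performed for monitoring purposes at 22 weeks and 38 weeks post transplant".
- Immune monitoring, on the earlier biopsy: "Histopathological samples will be taken at 5 months (protocol biopsy) in kidney transplant recipients randomised to the TR001 arm". Its purpose is given as follows: "This biopsy will confirm the ongoing safety of Treg therapy and ensure no evidence of subclinical rejection".
- Immune monitoring, on the later biopsy: "A 9-month protocol biopsy will be performed in all participants including the control arm". The stated reason is to allow a histological comparison between the arms.

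The Data analysis plan compares the arms on this endpoint by Kaplan-Meier curves, log-rank test, Cox hazard ratio and difference in 18-month proportions, at 20% significance with 80% confidence intervals. The Study design section adds: "Accordingly, outcome assessors and statisticians are not blinded". Under Primary outcome, borderline or suspicious reports are left to the treating physician to call.

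**The concern.** The sections agree on the schedule: five months is about week 22 and nine months about week 38. TR001 has two scheduled looks for rejection and control has one. The extra look is aimed at subclinical rejection. For-cause biopsies, which the article says are typically prompted by an unexplained creatinine rise, would tend to miss that kind of lesion.

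A silent lesion present at 22 weeks is recorded at once in TR001. In a control it is recorded only if it later becomes clinical or is still present at 38 weeks. If it resolves silently, it counts against TR001 and never against control. If it persists silently to 38 weeks, both arms record it, but TR001 does so 16 weeks earlier (38 − 22).

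The trial is meant to indicate whether a phase 3 trial is appropriate and to supply rates for its sample size. Only 3.6 to 6 control events are expected (30 × 12% to 30 × 20%), so one or two events due to surveillance can change the picture. Unblinded reading adds to this, because TR001 has one more biopsy open to judgement on borderline changes.

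**Working it through.** **1. The plan's own figure.** The Wilson interval width is 2z√[p(1−p)/n + z²/(4n²)] / (1 + z²/n), with z = 1.2816 (80%) and n = 30.

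- At 1/30: 2.5632 × √(0.001074 + 0.000456) / 1.0548 = 9.5%.
- At 15/30: 2.5632 × √(0.008333 + 0.000456) / 1.0548 = 22.8%.

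These round to the stated 10% and 23%. The stated precision is correct, but it describes sampling error within one arm and says nothing about unequal detection.

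**2. Inputs.** From the article: 30 per arm, 18-month (78-week) follow-up, 20% significance (taken as two-sided, since sidedness is not stated), expected control rejection 12–20%, and the biopsy schedule. Assumed, because the article gives no value: 16% for-cause rejection in both arms, 80% of it before week 26; 3% new subclinical rejection at week 38 in both arms; silent lesions at week 22 in s = 5, 10 or 15% of both arms; and the share of these that persists to week 38. There is no true difference between the arms.

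**3. Recorded rates if all 22-week lesions are transient.**

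- Control: 1 − 0.84 × 0.97 = 18.5%.
- TR001: 1 − 0.84 × 0.97 × (1 − s) = 22.6%, 26.7% and 30.7% for s = 5, 10 and 15%.

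**4. Log-rank test on all-biopsy rejection, by simulation.** The table gives the share of trials that flag TR001 as worse. With equal detection it is about 10%. Repeat runs differ by a point or two.

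| Persistence to week 38 | Across s = 5% to 15% |
|---|---|
| None | about 19% to 41% |
| Half | about 13% to 25% |
| All | about 10% to 12% |

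The last row shows that earlier recording alone, without extra events, hardly moves the test.

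**5. Exact check on 18-month proportions.** Let e be the assumed probability that the 22-week biopsy finds rejection not otherwise counted by month 18. The TR001 rate is then p + (1 − p)e, and the Pearson chi-square test is enumerated exactly for p = 12% to 20%.

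| e | Spurious difference (points) | Extra TR001 events | TR001 flagged as worse |
|---|---|---|---|
| 0 | 0 | 0 | 10.6–10.8% |
| 2% | 1.6–1.8 | 0.5 | 13.8–14.7% |
| 5% | 4.0–4.4 | 1.2–1.3 | 19.2–22.3% |
| 10% | 8.0–8.8 | 2.4–2.6 | 29.9–37.6% |
| 15% | 12.0–13.2 | 3.6–4.0 | 42.3–53.7% |

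Real benefit can also be hidden. With true rates of 20% (control) and 10% (TR001), the chance of a significant result favouring TR001 falls from 43.9% (e = 0) to 25.0% (e = 5%) or 12.8% (e = 10%).

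**6. Does dropping the 22-week findings remove the bias?** Count only for-cause biopsies and the 9-month biopsy, and assume that treatment after a 22-week finding clears the TR001 lesion while all control lesions persist. TR001 then records 18.5%, and control records 22.6%, 26.7% and 30.7%. The log-rank test falsely favours TR001 in about 20%, 27% and 39% of trials. This is close to a mirror image of the first row in step 4.

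**The case against.** The strongest objection is to the obvious remedy of redefining the primary endpoint on biopsies common to both arms. Step 6 shows that this can replace a bias against TR001 with one in its favour, in a trial that withholds induction, reduces maintenance immunosuppression and aims to confirm safety. That objection stands, and it is why the fix below leaves the primary endpoint as defined.

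Two further readings are tempting but not supported. A reader might infer that rejection present at 22 weeks can never be recorded in a control. It can be, for cause or at the shared 38-week biopsy, so only lesions that stay silent and resolve escape. A reader might also infer that event times in TR001 generally move forward by 16 weeks. That holds only for lesions that persist silently to week 38, and step 4 shows little effect from it.

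It can also be said that the trial is exploratory, openly not powered for definitive efficacy, and sized on per-arm precision. This lowers the stakes, but a systematic detection difference is not sampling error, and a lenient significance level does not absorb it. Finally, the article condenses a fuller protocol, and an analysis plan may already contain analyses by biopsy type. Their absence here is not the point. The point is that the endpoint, as stated, pools biopsies taken on unequal schedules and the arms are then compared on it.

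**Conclusion.** The concern holds as an ascertainment imbalance confined to the 22-week biopsy. The asymmetry is certain from the text, but its size is not. The result depends on the prevalence of silent lesions at 22 weeks, their persistence and their response to treatment, and the article gives none of these. Under the assumptions shown, the chance of wrongly flagging TR001 as worse ranges from about the nominal 10% (all lesions persist) to about 41% (15% prevalence, all transient).

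A reader might conclude that a phase 3 decision would be wrong for this reason alone. The documents do not support that: the bias could be negligible, and treating early findings could prevent later TR001 events and so act the other way. What does follow is that neither the all-biopsy nor the common-biopsy comparison is unbiased by itself. Together they indicate a plausible range.

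**What to change.** Keep all-biopsy rejection as the defined primary endpoint. Beside it, pre-specify two further analyses with equal prominence for the between-arm comparison:

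- (a) rejection on for-cause biopsies plus the 9-month biopsy common to both arms;
- (b) rejection on for-cause biopsies only.

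Report rejection found only on the 22-week biopsy separately, as a TR001 result. Base any statement about a difference in rejection, or about rates for phase 3 planning, on whether the three analyses agree.

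State in the plan that analysis (a) can err in favour of TR001 if treatment after a 22-week finding clears lesions that would persist in controls. The all-biopsy and common-biopsy results should therefore be read as indicating a range.

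The cost is some endpoint and analysis wording, two extra analyses, and a less clear-cut conclusion if they differ. There is no extra biopsy, no extra patient and no change in care, and the total stays at 60.

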**Methods and analysis:**

60 patients will be randomised on a 1:1 basis to Treg therapy (TR001) or standard clinical care (control). Patients in the TR001 arm will receive an infusion of autologous polyclonal ex vivo expanded Tregs 5 days after transplantation instead of standard monoclonal antibody induction. Maintenance immunosuppression will be reduced over the course of the post-transplant period to low-dose tacrolimus monotherapy. Control participants will receive a standard basiliximab-based immunosuppression regimen with long-term tacrolimus and mycophenolate mofetil immunosuppression. The primary endpoint is biopsy proven acute rejection over 18 months; secondary endpoints include immunosuppression burden, chronic graft dysfunction and drug-related complications.

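### For borderline or suspicious biopsies, a treating physician who knows the arm makes the diagnosis of rejection, and so apparently decides whether the primary event occurred

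*Protocol article*

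**What the plan says.** The Primary outcome section defines the endpoint: "The primary outcome is incidence of biopsy-confirmed acute rejection (BCAR) in the 18 months post transplantation". Events can come from protocol biopsies or from for-cause biopsies, which are taken at the responsible clinician's discretion. On reading, it says: "All biopsies performed will be reviewed and reported by the study pathologist using the internationally accepted Banff criteria". The next sentence makes an exception for ambiguous reports: "Whenever a biopsy is reported as suspicious for rejection or borderline changes, responsibility for a diagnosis of rejection lies with the treating physician".

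The Study design section explains the lack of blinding: "Treatment allocation will be open-label as pre-transplant venesection of blood for Treg manufacture in those allocated to the TR001 arm is required". It adds that venesecting control patients before major surgery would not be ethically appropriate, and concludes: "Accordingly, outcome assessors and statisticians are not blinded".

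The Data analysis plan reports at 20% significance with 80% confidence intervals. It uses the comparison to indicate whether a phase 3 trial would be appropriate.

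**The concern.** The endpoint is named as biopsy-confirmed. For borderline or suspicious reports, however, the article gives no histological threshold that settles whether the case counts. It hands the diagnosis to the person treating the patient, who knows the arm.

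That person has arm-specific reasons to lean either way. TR001 patients receive no induction antibody and have their immunosuppression reduced, which could make a physician quicker to call rejection. Hope for the cell therapy could make the same physician slower. Because the direction is unknown, the bias cannot be corrected afterwards.

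The reason given for open-label treatment is the venesection. It explains why patients and clinicians know the arm. It does not explain why the ambiguous biopsies must be classified for the endpoint by someone who knows it.

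At stake are the two things the trial is meant to deliver: rejection rates for planning phase 3, and an indication of whether phase 3 is worthwhile.

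**Working it through.** **Inputs from the article.** 60 patients randomised 1:1, so n = 30 per arm (Study design). Expected rejection on the standard anti-CD25 regimen is 12%–20% over 18 months; for Treg therapy there is little data, and rates of 0% and 27% are cited (Sample size calculation). Significance level 20%, 80% intervals (Data analysis plan).

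**Assumptions.** The test is two-sided (the article does not say). An uncorrected chi-square test on the 18-month proportions stands in for the planned log-rank test. The share of patients whose only positive finding is a borderline biopsy is not given; I take b = 5% to 20%, the same in both arms.

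**1. The plan's own figure.** The 80% Wilson width is 2z·√(p(1−p)/n + z²/(4n²)) / (1 + z²/n), with z = 1.2816.
- 1/30: 9.5 points
- 4/30: 16.0 points
- 5/30: 17.3 points
- 6/30: 18.5 points
- 15/30: 22.8 points

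This reproduces the stated range of 10% to 23%. The precision statement is not in dispute.

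**2. Events and the weight of one patient.** Control arm: 30 × 0.12 = 3.6 and 30 × 0.20 = 6, so about 4 to 6 events. TR001, from the cited rates: 30 × 0 = 0 to 30 × 0.27 = 8.1. One patient is 1/30 = 3.3 points.

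**3. How many calls cross the 20% level.**

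| TR001 v control | Calls changed | p |
|---|---|---|
| 5/30 v 5/30 | none | 1.00 |
| 4/30 v 5/30 | 1 | 0.72 |
| 2/30 v 5/30 | 3 | 0.23 |
| 1/30 v 5/30 | 4 | 0.085 |
| 10/30 v 5/30 | 5, other direction | 0.136 |
| 1/30 v 4/30 (from 4 v 4) | 3 | 0.16 |

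In the last row the difference is −10.0 points, 80% CI −19.0 to −1.0.

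**4. False-positive rate under arm-dependent calling.** Let 12% in each arm have clear-cut rejection and let q be the proportion of borderline cases called rejection. The observed rate is then 0.12 + b·q. For b = 10% and q = 25% in TR001 and 75% in control, the rates are 0.12 + 0.10 × 0.25 = 0.145 and 0.12 + 0.10 × 0.75 = 0.195. The probability that the nominal 20% test rejects is summed over all pairs of binomial counts with n = 30.

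| b | q 50% v 50% | q 25% v 75% | q 0% v 100% |
|---|---|---|---|
| 5% | 21% | 23% | 28% |
| 10% | 22% | 28% | 43% |
| 15% | 22% | 33% | 60% |
| 20% | 21% | 39% | 75% |

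Histology is the same in both arms throughout, so every rejection is false. The first column is the test's own small-sample level. The excess over it is due to arm-dependent calling.

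**5. With a fixed rule.** If no borderline case counts, both rates are 12% and the test rejects in 21%. If all count, both rates are 0.12 + b (17% to 32%) and it rejects in 21–22%. Either rule removes the inflation.

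**The case against.** **The article is a condensed protocol.** It is based on protocol V.7.0, and that document or the SAP may hold a counting rule for borderline cases. The article assigns the diagnosis to the physician; it does not say in terms that this diagnosis is counted as the primary event. That is why the point says apparently. But the sentence stands under Primary outcome, directly after the sentence on who reads the biopsies, and nothing else there says how such reports count. It is a stated rule, not a missing detail.

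**The effect may be small.** One changed call gives p = 0.72, and 3.3 points is well inside an 80% interval 16 to 18.5 points wide. At a 5% borderline share, a 25% v 75% split lifts the false-positive rate only to 23%. This stands, and it limits the severity.

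**The trial is exploratory and declares its open-label design as a limitation.** Also true. But the rates and the comparison feed the phase 3 decision, and declaring a bias does not remove one that a counting rule could avoid.

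**Stronger readings that the article does not support.**
- A reader might infer that the study pathologist reads with knowledge of the arm. The article says only that outcome assessors are not blinded; it does not say whether the pathologist is masked.
- A reader might apply 4 to 6 events to both arms. The 12%–20% figure is for the control regimen only.
- A reader might take a 10-point shift as the expected effect. It needs 3 borderline patients in 30 (an assumed 10%) and every one called the same way in a single arm, so it is a ceiling.
- A reader might add the biopsy that only one arm receives: "Histopathological samples will be taken at 5 months (protocol biopsy) in kidney transplant recipients randomised to the TR001 arm". That is unequal ascertainment, a separate matter: clear-cut rejection found there would count under any reading rule.

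**Conclusion.** The concern holds for borderline and suspicious reports. As written, a physician who knows the arm makes the diagnosis on which the primary event apparently rests, and identical histology could be counted differently by arm, in an unknown direction.

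With moderate differential calling (25% v 75%), the false-positive rate of the nominal 20% test rises from about 21–22% to 23–39% as the assumed borderline share goes from 5% to 20%. The 0% v 100% column is an extreme bound, not a forecast. These figures rest on 12% clear-cut rejection in both arms, equal borderline shares, a two-sided test, and chi-square in place of log-rank. The article gives neither the borderline share nor how physicians call such cases, so the actual size is not known.

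This should be fixed. The article does not support the inference that the primary result is already invalid or that it favours either arm.

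**What to change.** Define the primary event by a prespecified Banff category taken from the study pathologist's report and applied identically in both arms. Handle borderline or suspicious reports by one fixed rule in the primary analysis and by the opposite rule in a sensitivity analysis. Record the treating physician's diagnosis as a separate variable and report it alongside; decisions on care stay with the physician.

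Where practicable, assign the category used for the endpoint from slides labelled without the arm. Whether the reader who issues live clinical reports can also be masked is not clear from the article, so this part is conditional. The fixed rule does not depend on it.

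**Cost.** Wording in the protocol and SAP, one extra data field and one extra analysis; no extra biopsy, and the fixed rule needs no extra reader. The primary rate may differ from clinically diagnosed rejection. If borderline cases are not counted and physicians would have called half of them rejection, the primary rate is 12% against 0.12 + 0.05 × 0.5 = 14.5% up to 0.12 + 0.20 × 0.5 = 22%, so 2.5 to 10 points lower over the assumed range. That can be a noticeable gap, hence the need to report both.

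The change does not equalise biopsy frequency. The TR001-only 5-month biopsy and the discretionary for-cause biopsies need their own treatment.
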